### Sample size calculations

The planned sample size is 50 participants, with participants randomly allocated to either a treatment group (*n* = 25) or a waitlist control group (*n* = 25). Power calculations are based on an estimated between-group effect size of 0.92 based on a meta-analysis of iCBT compared to controls [92] with alpha set at 0.05 and power at 0.8. A minimum sample of 20 participants per group is required to detect this effect size. An additional 5 participants per group will be recruited to account for expected attrition based on our pilot trial [33].

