## Background

Social anxiety disorder (SAD) is a highly prevalent and often debilitating condition in which social interactions or being observed triggers intense fear or anxiety about being negatively evaluated or rejected by others [1]. SAD is estimated to impact approximately 14.4% of Australians between the ages of 18–85 over a 12-month period [2] and has been found to be more prevalent in women, particularly during adolescence [1]. Left untreated, SAD can lead to significant social, occupational, educational, and functional impairment for the individual [3], as well as social and economic impacts on wider society [4]. SAD has been found to be highly comorbid with other mental health conditions, particularly major depressive disorder (MDD), which SAD often precedes [5], and personality disorders, with co-occurrence of SAD and avoidant personality disorder estimated to range from 22 to 89% [6–8]. Notably, both comorbid depressive symptoms [9] and personality pathology [10] can exacerbate the severity of social anxiety symptoms and impact treatment response.

Clinical practice guidelines recommend cognitive behaviour therapy (CBT) as the preferred first-line treatment for SAD [11]. CBT has been shown to be efficacious when delivered in both face-to-face and online formats [11], with some studies finding that internet CBT (iCBT) is just as, if not marginally more, effective than face-to-face CBT, as well as more accessible [12, 13]. A systematic review [14] of over 20 randomised controlled trials (RCTs) found that iCBT (when delivered over 9 or 10 weeks) had a moderate positive average pooled between-group effect size (*g* = − 0.55) on patients’ social anxiety symptoms relative to control groups, increasing to a large pooled between-group effect size (*g* = − 0.79) when compared to a waitlist control group. Treating social anxiety symptoms using iCBT has also been found to have positive effects for treating comorbid MDD and depressive symptoms [15, 16].

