### Limitations of the study and future research

The results of this study should be interpreted with consideration of some limitations. Firstly, the use of a passive (waitlist) versus active control group means that while it is discouraged for participants to commence other therapies or medication during the waiting period, we are unable to control for other care they receive during this time. Future studies would benefit from comparing the treatment to an active control condition such as a digital placebo program or a psychoeducation control group. Future research should also compare this intervention to standard-paced iCBT or intensive face-to-face CBT. While our predictor analyses will provide some initial understanding as to whom this intensive approach is most suited, a RCT comparing the intensive and standard-paced formats (and to traditional face-to-face formats) will provide further clarification as to who benefits most from these diverse treatment approaches. A further limitation relates to the relatively short follow-up period; future studies would be strengthened by a longer-term follow-up period (e.g. 3 months or longer) to measure the longer-term impact of the intervention. In addition, our power calculations have been informed by meta-analyses of standard paced iCBT [92] and may have overestimated the expected between-group effect size. Future studies should consider using minimal important clinical differences to inform sample size calculations, to ensure similar studies are powered to detect changes that are not only statistically significant, but clinically meaningful.

Second, the risk of bias cannot be completely eliminated in the collection of some study data. It is not feasible to blind researchers to participant group allocation follow-up interviews. We will also rely on participant self-report to measure some engagement variables (length of time spent reading module material or practising skills) so this may be inaccurate. Relatedly, as the treatment is completed by participants online rather than in vivo with a clinician, it is not possible for clinicians to model the therapy skills (e.g. exposure). As such, it will be unclear if participants are implementing these skills with complete fidelity to the program instructions.

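### The sample size is powered at alpha 0.05, but each co-primary scale is tested at 0.025: at the assumed effect of 0.92, 20 per group gives 72% power per scale, not 80%, and less at the 0.79 cited in the Background

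*Protocol article*

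**What the plan says.** Under Sample size calculations, the protocol article plans on an "estimated between-group effect size of 0.92 based on a meta-analysis of iCBT compared to controls", "with alpha set at 0.05 and power at 0.8". From this it concludes: "A minimum sample of 20 participants per group is required to detect this effect size". It then adds an allowance for loss ("An additional 5 participants per group will be recruited to account for expected attrition based on our pilot trial"), which brings the total to 50, or 25 per group.

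Under Statistical analysis, SIAS and SPS are co-primary, and a Bonferroni correction sets the significance level at 0.025 for these two scales. The same section plans linear mixed models with a random intercept, between-group comparisons at post-treatment and follow-up, and Hedges' g with 95% confidence intervals.

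The Background cites a systematic review of more than 20 randomised trials of iCBT delivered over 9 or 10 weeks. Its pooled effect in absolute value is 0.55 against control groups overall, "increasing to a large pooled between-group effect size (*g* = − 0.79) when compared to a waitlist control group". The comparator in this trial is a waitlist.

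The limitations section says that the power calculation drew on standard-paced iCBT and "may have overestimated the expected between-group effect size". It gives no alternative value and no power figure.

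**The concern.** Two features of the sample size statement do not fit the rest of the article.

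The first is the significance level. The calculation uses 0.05, while the test that decides each co-primary outcome uses 0.025. The stated power therefore belongs to a test that will not be carried out on either scale.

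The second is the effect size. The planning value of 0.92 is larger than both pooled figures in the Background, including the one for the same type of comparator. Those figures come from treatment over 9 or 10 weeks, and this trial tests a one-week format. The article does not explain why 0.92 was preferred.

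What is at stake is how a result is read. The article presents this trial as a step towards deciding whether a larger, more costly comparison is warranted. If SIAS or SPS misses significance, readers will judge the miss against the stated 80%. If the true figure per scale is lower, the miss says less against the programme than it appears to.

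**Working it through.** **Inputs.** Effect 0.92, alpha 0.05, power 0.80, 20 per group and 25 per group: Sample size calculations. Alpha 0.025 per scale: Statistical analysis. Effect 0.79 against waitlist: Background. The article does not state sidedness; two-sided is assumed because it reproduces the stated number.

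**Formula.** For a two-sample t-test with n per group and standardised difference d, the degrees of freedom are 2n − 2 and the noncentrality is d × √(n/2). Power is the probability that a noncentral t variable falls beyond the two-sided critical value.

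**Step 1: the plan's own figure.** With d = 0.92 and n = 20, the noncentrality is 0.92 × √10 = 2.909 on 38 degrees of freedom. At alpha 0.05 the critical value is 2.024 and power is 80.9%. Solving for 80% gives n = 19.55, rounded up to 20. A one-sided test would need only 16. An attrition allowance of 5 in 25 is 20%, and 20/(1 − 0.20) = 25. The stated figures reproduce.

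**Step 2: the alpha that will be used.** With the same noncentrality of 2.909, the critical value at alpha 0.025 is 2.334 and power falls to 71.6%. Solving for 80% gives n = 23.76, so 24 per group. With all 25 per group the noncentrality is 3.253, the critical value is 2.314 and power is 82.3%.

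**Step 3: the Background's waitlist figure.** With d = 0.79 and n = 20, the noncentrality is 0.79 × √10 = 2.498; with n = 25 it is 2.793.

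Unadjusted power per scale:

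| Effect | Alpha | 20 per group | 25 per group | n per group for 80% |
|---|---|---|---|---|
| 0.92 | 0.05 | 80.9% | 89.0% | 20 |
| 0.92 | 0.025 | 71.6% | 82.3% | 24 |
| 0.79 | 0.05 | 68.3% | 78.1% | 27 |
| 0.79 | 0.025 | 56.9% | 68.4% | 32 |

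**Step 4: baseline adjustment.** If the comparison adjusts for a baseline score that correlates r with the outcome, the effective difference is about d/√(1 − r²). The article gives no r, so 0.5 to 0.7 is an assumption. At d = 0.79 the effective difference is 0.79/√0.75 = 0.912 for r = 0.5 and 0.79/√0.51 = 1.106 for r = 0.7. With 20 per group at alpha 0.025, power is then 71% and 87%. At d = 0.92 the same step gives 84% and 96%.

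**The case against.** The strongest reply has four parts.

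*The arithmetic is right and the effect size is a judgement.* This stands. A reader might infer that the calculation is wrong, or that the article contradicts itself on the effect size. The documents support neither. Twenty per group gives 80.9% on the stated inputs. The values 0.92 and 0.79 come from different cited reviews, and nothing in the article says that one supersedes the other. The article also does not say what kind of controls lie behind 0.92. Possible overestimation is disclosed, though without a number. Preferring 0.79 is therefore a matter of assumption, which is why it belongs in the text as a sensitivity value and not as a correction.

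*The low figures are pessimistic.* This stands in part. A reader might infer that a significant result on a given scale is little better than a coin toss. That reading needs the smaller effect, only 20 contributing per group and no use of baseline, all at once. In the pilot, 15 of 16 participants completed all modules. That is module completion and not assessment retention, but if 23 per group gave data, unadjusted power at alpha 0.025 would be 78% at 0.92 and 64% at 0.79. The planned mixed model may also gain from baseline data, although the sample size section claims no such gain.

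*The Bonferroni split suggests that success on either scale is enough.* If so, the chance of at least one significant result is higher than power per scale. In 100,000 simulated trials with equal effects on both scales and an assumed correlation between them of 0.5 to 0.8, it was about 81% to 86% at 0.92 with 20 per group, and about 67% to 73% at 0.79. The article does not define its 80% in this way, and the calculation at alpha 0.05 is a single-outcome one. The restated text should say which is meant.

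*Intervals are already planned.* This stands. Hedges' g with 95% confidence intervals lets a null result be read properly, so a separate pledge on that would add little. No passage says that a non-significant result would be taken as absence of effect.

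None of these replies reconciles 0.05 in one section with 0.025 in the other.

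**Conclusion.** The point holds as a mismatch of significance level, with an optimistic effect size as a second, conditional part.

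The firm part needs no choice between reviews. At the sponsor's own 0.92, testing each scale at 0.025 lowers power per scale with 20 per group from 81% to 72%, and the minimum for 80% rises from 20 to 24 per group. The planned 25 per group would still give 82%, but only with almost no loss.

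The conditional part is that at 0.79, power per scale at alpha 0.025 is 57% with 20 and 68% with 25 per group.

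Both parts assume a two-sided, unadjusted comparison at post-treatment, with power counted for one scale. Adjustment for baseline could bring the figures back near or above 80%, depending on a correlation that the article does not give. The flaw lies in the stated power, not in the planned tests or in the validity of the comparison.

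**What to change.** Restate the Sample size calculations section without changing enrolment, since the Trial status section reports that recruitment was completed in June 2024:

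- Give power per scale at alpha 0.025 for 20 and 25 per group: 72% and 82% at 0.92, with 57% and 68% at 0.79 as a sensitivity value. Describe 80.9% as the figure at alpha 0.05.
- State in a sentence why 0.92 was chosen over the waitlist figure in the Background.
- State whether power refers to each scale or to at least one of the two.
- Add that baseline adjustment could recover much of the loss (at 0.79, alpha 0.025 and 20 per group, 71% to 87% for an assumed baseline correlation of 0.5 to 0.7), labelled as resting on an assumed correlation.

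The cost is wording only. The downside for the sponsor is that the stated power becomes less favourable. The restatement should be presented as a correction of the planning assumptions, not as power computed from the observed results.

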### Statistical analysis

All analyses will be undertaken using intention-to-treat approach. Linear mixed models, with a random intercept for subject will be used to analyse primary and secondary outcomes, and covariances matrixes used to assess relationships between variables. This approach will be used to manage missing data and account for correlation between repeated measures. Before conducting the analyses, patterns of missing data will be assessed through data visualisation, and Little’s Missing Completely at Random (MCAR) test to determine whether the data are missing at random. If there are significant group differences (as determined by independent samples *t*-tests) in the amount of time elapsed between the intake interview and completion of baseline measures, this variable will be included as a covariate in the linear mixed models. Planned contrasts will be used to compare pre- and post-treatment, and pre-treatment and 1-month follow-up, and planned pairwise comparisons will be used to compare between-groups at post-treatment and follow-up. To control for the risk of type 1 error with a co-primary outcome, the alpha level for significance will be adjusted using a Bonferroni correction (alpha set at 0.025 to determine statistical significance for the SIAS and SPS co-primary outcome measures). Linear mixed models will be utilised to test the predictors of treatment outcome. Within- and between-group effect sizes will be calculated using Hedges’ *g* (with 95% confidence intervals) to estimate the within-group changes from baseline to post-treatment, and baseline to follow-up, and between-group differences on primary and secondary outcome measures at post-treatment and follow-up.

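### The trial is sized at alpha 0.05 but each co-primary scale is tested at 0.025, so with 20 analysed per arm the power is about 72% per scale, not 80%

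*Protocol article*

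**What the plan says.** Protocol article, Sample size calculations: "Power calculations are based on an estimated between-group effect size of 0.92", taken from a meta-analysis of iCBT against controls, "with alpha set at 0.05 and power at 0.8. A minimum sample of 20 participants per group is required to detect this effect size". The plan is to recruit 25 per arm, 50 in total, because "An additional 5 participants per group will be recruited to account for expected attrition based on our pilot trial".

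Protocol article, Statistical analysis: because there are two co-primary scales, a Bonferroni correction applies, with "alpha set at 0.025 to determine statistical significance for the SIAS and SPS co-primary outcome measures".

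The sample size paragraph mentions neither the correction nor the second scale. The Limitations section concedes that the power calculation "may have overestimated the expected between-group effect size" but says nothing about alpha. The Background separately cites a pooled effect of 0.79 for iCBT "when compared to a waitlist control group", which is this trial's comparator.

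**The concern.** A sample size calculation should describe the test that decides the primary question. Here the calculation uses twice the significance level of that test, so the stated power is too high and the stated minimum too low for either scale taken alone.

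The Trial status section says recruitment and data collection are finished and analysis is underway, so the number of participants is fixed. What remains open is how the results are read. If the results paper repeats 80% power with a minimum of 20 per arm, a non-significant SIAS or SPS result will look stronger evidence against efficacy than it is. With 20 per arm and a true difference of 0.92, a given scale is missed about 28% of the time at 0.025 (1 − 0.716), against 19% at 0.05 (1 − 0.809).

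**Working it through.** **Inputs.** From Sample size calculations: d = 0.92, alpha 0.05, power 0.80, minimum 20 per arm, 25 recruited per arm. From Statistical analysis: alpha 0.025 per scale. From Randomisation and allocation procedures: 1:1 allocation. Sidedness is not stated and is inferred below.

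**Method.** Two-sample t-test with n per arm. Degrees of freedom are 2n − 2, non-centrality is d·√(n/2), and two-sided power is the probability that the non-central t variable exceeds the critical value in absolute size.

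**Step 1: reproduce the article's figure.** With n = 20, non-centrality is 0.92 × √10 = 2.909 on 38 degrees of freedom. At two-sided 0.05 the critical value is 2.024 and power is 0.809. With n = 19 power is 0.788, so 20 is the smallest n that reaches 80%. A one-sided 0.05 test would need only 16. The stated 20 is therefore the two-sided 0.05 result with no adjustment for two scales.

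**Step 2: apply the alpha of the analysis.** At two-sided 0.025 with n = 20 the critical value is 2.334 and power is 0.716. Across the possible analysed numbers, for d = 0.92:

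| Analysed per arm | Power at 0.05 | Power at 0.025 |
|---|---|---|
| 20 (all five extra lost) | 0.809 | 0.716 |
| 23 (about the pilot's loss: 25 × 15/16 = 23.4) | 0.862 | 0.785 |
| 24 | 0.877 | 0.805 |
| 25 (no loss) | 0.890 | 0.823 |

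The minimum for 80% at 0.025 is 24 analysed per arm. A normal approximation gives 19 per arm at 0.05 and 23 at 0.025, with power 0.748 at n = 20, so the conclusion does not depend on the method.

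**Step 3: detectable difference.** Solving for d at 80% power with n = 20 gives 0.91 at alpha 0.05 and 1.01 at alpha 0.025. The second exceeds the assumed 0.92.

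**Step 4: two scales together.** The article gives no SIAS–SPS correlation, so a range is assumed. Simulated two-arm trials with n = 20, d = 0.92 on both scales and each tested at 0.025 gave:

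| Assumed correlation | At least one significant | Both significant |
|---|---|---|
| 0.5 | 0.86 | 0.57 |
| 0.8 | 0.81 | 0.63 |
| 0.9 | 0.78 | 0.65 |

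**Step 5: sensitivity to the effect size.** At the waitlist effect of 0.79 cited in the Background, power per scale at 0.025 is 0.569 with 20 per arm and 0.684 with 25. The minimum for 80% would be 27 per arm at 0.05 and 32 at 0.025.

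**The case against.** - **A Bonferroni split suits a rule under which either scale can succeed.** On that reading power with 20 per arm is about 78% to 86%, and the 80% broadly survives. This is a fair reading, but the article does not state the rule or say that the 80% refers to it, and its n is exactly that of one test at 0.05. The point stands as a reason to state the rule. If both scales had to succeed, no Bonferroni correction would be needed, so the last column of Step 4 carries little weight.
- **Twenty per arm is the low end.** Twenty-five are recruited, the analysis is intention-to-treat with mixed models that use partial data, and 15 of 16 pilot participants completed all modules. That last figure is module completion, not assessment completion. If at most one participant per arm is lost, per-scale power is above 80%. This justifies giving a range, but 20 is the article's own post-attrition figure, and recruits set aside for attrition cannot also pay for the correction.
- **The mixed model may be more precise than a t-test.** That is possible, but the calculation claims no such gain and gives no correlation to support one.
- **The effect size limitation is already disclosed, and 0.79 and 0.92 come from different sources that cannot be compared here.** This is accepted. The 0.79 figures are only a sensitivity check, and the finding does not rest on them.
- **The harm is limited.** Type I error is controlled, and the plan commits to effect sizes with 95% confidence intervals, which would show how imprecise a null result is. This lowers the gravity but does not make the stated power right.

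**Conclusion.** The concern holds. The arithmetic behind 20 per arm is correct for a single two-sided test at 0.05, but that is not the test the Statistical analysis section prescribes. At the prescribed 0.025, per-scale power for d = 0.92 is 72% with 20 analysed per arm, 79% with about 23, and 82% with all 25. The minimum for 80% is 24, not 20.

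These figures assume a two-sided, two-sample t-test on a standardised difference, which is the method that reproduces the article's number. The shortfall is per scale. For success on at least one scale it largely disappears at 20 per arm unless the scales correlate very highly. The validity of the planned test and its estimates is not affected. What needs correcting is the stated power and the stated minimum.

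**What to change.** Replace the calculation with one at the level that will be used, in the SAP and the results paper, for example: *At two-sided alpha 0.025 per scale and a standardised difference of 0.92, power per scale is 72% with 20 analysed per arm and 82% with 25; 24 analysed per arm are needed for 80%; with 20 per arm the difference detectable with 80% power is 1.01.*

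Add one sentence saying whether the 80% was meant for each scale or for at least one, and what counts as success on the primary question. If it was meant for at least one, give that power with the assumed SIAS–SPS correlation. As an optional sensitivity line beside the existing limitation on effect size, give 57% (20 per arm) to 68% (25 per arm) per scale at the waitlist effect of 0.79.

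The cost is one paragraph and a less favourable stated power. No extra enrolment and no change to the analysis are needed.

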### Dissemination

When data analysis is finalised, a summary of research findings will be emailed to all participants and made available on the Black Dog Institute website. The research study will also be prepared for publication in relevant peer-reviewed scientific journals and presented at academic conferences. In all papers, numerical data will be aggregated, and no individual participants will be identifiable. All qualitative data will also be non-identifiable.

### Lived experience input

During the planning of this study, the investigator team consulted with a small group (*n* = 5) of members of the Black Dog Institute Lived Experience advisory network. Lived experience advisors provided recommendations regarding the preferred name of the program, the timing and format of the clinician support, the preparation process, and the advertising material, as well as the choice, type (e.g. qualitative, and quantitative), and focus of the assessment measures.

